### Measures

All seven questionnaires will include the following constructs: off-job crafting, subjective vitality, mental fatigue, stress, health status, private life satisfaction, job satisfaction, work engagement, family role performance, job performance, organizational citizenship behavior, basic need satisfaction, satisfaction of psychological needs, home demands, job demands and job crafting. Additionally, the baseline questionnaire will include need strengths, proactive personality, focus on opportunities, Selection, Optimization, and Compensation strategies and background variables. Both the baseline and the fourth weekly questionnaire will additionally measure participation in different off-job activities.

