#### Background variables

We ask the participants to state their age, gender, highest level of formal education, family status, living situation, type of work, weekly working hours, and tenure.

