### Statistical analyses

#### Sample size calculation

The G*POWER software [64] was used to determine the minimum number of participants necessary to guarantee sufficient power of the study. Assuming an effect size of .25 (medium), alpha = .05 and power = .80, the required sample size is 64 participants per group to determine a significant difference between the intervention and the waitlist control group. Taking into account potential non-response and loss to follow-up, we aim to recruit at least 200 employees to ensure an adequate sample size.

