#### Basic analyses

All basic analyses are carried out with SPSS 25 [65]. Two-tailed significance level of < .05 will be considered statistically significant. Baseline characteristics of the participants are analyzed using descriptive statistics. Independent samples t-tests or chi-square tests are applied to check whether randomization was successful or whether there were systematic differences between the two groups. Preliminary analysis will be performed, including calculating descriptive statistics (i.e., means, standards deviations), factor analyses for all the scales, internal reliability calculations (Cronbach’s *α*) and bivariate correlations (Pearson’s *r*) between the study variables.

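### Baseline significance tests cannot show whether randomisation succeeded; describe balance instead, and fix adjustment for the baseline outcome and organisation in advance

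*Protocol article*

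**What the plan says.** The Basic analyses section of the protocol article states that "Independent samples t-tests or chi-square tests are applied to check whether randomization was successful or whether there were systematic differences between the two groups". The same section sets the threshold: "Two-tailed significance level of < .05 will be considered statistically significant". It also plans descriptive statistics for baseline characteristics. It does not name the variables to be tested, mentions no multiplicity correction, and ties no action to a significant or non-significant result.

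The candidate variables are listed elsewhere:
- Background variables: "age, gender, highest level of formal education, family status, living situation, type of work, weekly working hours, and tenure".
- Measures, repeated constructs: "All seven questionnaires will include the following constructs: off-job crafting, subjective vitality, mental fatigue, stress, health status", followed by eleven more.
- Measures, baseline only: "the baseline questionnaire will include need strengths, proactive personality, focus on opportunities, Selection, Optimization, and Compensation strategies and background variables".
- Measures, activities: "Both the baseline and the fourth weekly questionnaire will additionally measure participation in different off-job activities".

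Study population and recruitment describes random assignment within each organisation, worded as an aim. Effect evaluation plans multilevel models of change over measurement points that include baseline, and a comparison of that change between groups. It does not say whether the baseline outcome is conditioned on, or whether organisation enters the model.

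**The concern.** A significance test asks whether a difference is larger than chance would readily produce. If allocation was random, chance is the only source of baseline differences among those randomised. A p-value below .05 is then a false alarm by construction. A p-value above .05 does not show balance either, because the test misses differences of moderate size.

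The article nevertheless gives the test the purpose of judging whether randomisation worked. A sound trial could be reported as having failed randomisation, or an imbalanced sample as having passed. Leaving the consequence of a significant result open also leaves room for covariates chosen after the data are seen, although the article plans no such step.

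**Working it through.** **The plan's own figure.** The article gives no error rate for the baseline tests. The nearest figure is the sample size: "Assuming an effect size of .25 (medium), alpha = .05 and power = .80, the required sample size is 64 participants per group". A two-sided t-test with d = 0.5 needs 63.77, so 64 per group; a two-group F-test with f = 0.25 needs 127.5 in total, so 128, or 64 per group. The 64 is reproduced when .25 is read as Cohen's f (d = 0.5).

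**Number of candidate variables.** 16 repeated constructs + 4 baseline-only constructs + 1 activity scale + 8 background variables = 29.

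**False alarms under correct randomisation.** For k independent tests at .05, P(at least one) = 1 − 0.95^k.

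| Variables tested | k | Expected false alarms (0.05k) | P(at least one) |
|---|---|---|---|
| Background only | 8 | 0.40 | 33.7% |
| Repeated constructs only | 16 | 0.80 | 56.0% |
| Background + repeated constructs | 24 | 1.20 | 70.8% |
| All listed | 29 | 1.45 | 77.4% |

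The probability passes one half between 13 tests (48.7%) and 14 (51.2%).

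The article gives no correlations among the variables, so these are assumed. A simulation with equally correlated normal test statistics (200,000 draws) gives:
- 8 variables, all correlated at 0.5: 25%.
- 29 variables, all correlated at 0.5: 50%.
- 8 independent background variables plus 21 scales correlated at 0.1, 0.3 or 0.5: 76%, 70% or 62%.

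**Differences that pass.** The smallest observed standardised difference that reaches p < .05 is t(.975, 2n−2) × √(2/n).
- n = 100 per group: 0.279 SD. This takes the recruitment target, "we aim to recruit at least 200 employees to ensure an adequate sample size", split 1:1; the ratio is an assumption.
- n = 64 per group: 0.350 SD.

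If there were a genuine systematic difference of 0.25 SD, the test would flag it 42% of the time at 100 per group and 29% at 64 per group.

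**What an imbalance does to the effect estimate.** For one before-and-after contrast with baseline correlation r and observed imbalance D, an unadjusted change contrast moves by (1 − r) × D. With D = 0.28, the shift is 0.20 SD at r = 0.3, 0.14 SD at r = 0.5 and 0.08 SD at r = 0.7 (r is assumed). These take the largest imbalance that still passes. A chance imbalance of one standard error at 100 per group is √(2/100) = 0.14 SD, and at r = 0.5 it moves the contrast by 0.07 SD. Over repeated randomisations these shifts average zero, and the standard error already includes them.

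**Precision.** For the same single contrast, the variance is proportional to 2(1 − r) for a change score and 1 − r² with baseline as a covariate. The ratio of the second to the first is (1 + r)/2: 0.65, 0.75 and 0.85 at r = 0.3, 0.5 and 0.7. This illustrates the gain if the planned model does not already condition on baseline; it is not a calculation for the full multilevel model.

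**The case against.** The best defence is that this is a conventional preliminary check on which no estimate depends. That is right: the article attaches no covariate selection, exclusion or change of model to the result. A reader might infer that the test is a decision rule governing the analysis, but the text describes only a check.

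A reader might also infer that a correct randomisation would be called a failure most of the time. That depends on how many variables are tested, which the article leaves open. The sentence before the tests concerns participants' baseline characteristics, and it can fairly be read as the 8 background variables, for which the chance is 25–34%. Nor does the article say that a single significant result means failure.

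A third tempting reading is that imbalance up to 0.35 SD goes unadjusted and biases the effect by about 0.17 SD (0.5 × 0.35), a third of d = 0.5. The documents do not support it. The effect evaluation models change with baseline among the measurement points, and no unadjusted comparison of post-intervention scores is planned. The 0.17 SD is a chance shift at the edge of the tail in one realised sample, using 64 per group although recruitment aims higher. An article may also leave covariate lists to a fuller plan, so their absence is not the error here.

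Finally, a search for systematic differences has some purpose. Random assignment is worded as an aim. Under Study design, the intervention group receives its preparatory task around the baseline questionnaire, so allocation may be known before some baselines are completed, and response could differ by group. That stands, but the detection rates of 42% and 29% show that a p-value threshold is a weak tool for it. What the defence does not rescue is the stated purpose of the test.

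**Conclusion.** The point holds in a limited form. The article states, rather than omits, a use of significance tests that cannot deliver the intended conclusion. Under random allocation a significant baseline difference says nothing about whether randomisation worked, and a non-significant one does not establish balance.

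The chance of at least one false alarm runs from about 34% (8 variables) to about 77% (29 variables) with independent tests, and from about 25% to 50% if all are correlated at 0.5. Differences up to about 0.28 SD (100 per group, 1:1 assumed) or 0.35 SD (64 per group) pass. The variable count, the correlations and the allocation ratio are assumptions, because the article does not fix them.

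The consequence is an invalid statement about randomisation and, if the models do not condition on baseline, some lost precision. It is not bias in the planned test of the intervention effect, and it does not threaten the validity of the trial.

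**What to change.** In Basic analyses, replace the tests and the verdict on randomisation with baseline means, SDs (or proportions) and standardised differences by group. Address possible departures from random assignment by documenting how allocation was carried out in each organisation and by reporting baseline questionnaire response by group.

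In Effect evaluation, state in advance that each between-group model adjusts for the baseline value of its outcome, either as a covariate or through a common baseline mean constrained to be equal across groups, and for organisation, the unit within which allocation is intended. Apply this whatever imbalance is observed, so that no covariate depends on a baseline p-value.

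The cost is a little analysis wording and a few degrees of freedom for organisation. No new data are needed: the outcomes are already measured at baseline, and recruitment runs through the organisations.

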#### Effect evaluation

We will use multilevel modelling techniques to test the change in outcome variables within subjects across seven measurement points before, during and after the intervention (i.e., within subject effect of participating in off-job crafting intervention). We will use Bliese and Ployhart’s [66] approach to estimate multilevel models in R, using the NLME library written by Pinheiro and Bates [67]. Additionally, we will test how participation in off-job intervention compared to control group affects the change in outcome variables across time (i.e., between subjects’ effect of the intervention compared to control group).

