The aim of this intervention study is to evaluate the effectiveness of a hybrid off-job crafting intervention compared to a waitlist control group on off-job crafting behaviors, psychological need satisfaction, well-being and performance. We hypothesize that off-job crafting can be stimulated in the intervention group compared to a waitlist control group (between-person difference), and that people will engage more often in off-job crafting during and after the intervention period than before (within-person changes). Moreover, we expect that increased off-job crafting will lead to higher well-being and performance during and after the intervention (compared to baseline and to the control group). We hypothesize that as the result of the intervention, participants will report higher basic need satisfaction and satisfaction of psychological needs during and after the intervention compared to baseline and to the waitlist control group. In terms of work-related well-being outcomes, we expect that participants will report higher work engagement and job satisfaction during and after the intervention compared to baseline and to the waitlist control group. In the non-work domain, we hypothesize that participants will report higher subjective vitality, private life satisfaction and health status and lower stress and mental fatigue levels during and after the intervention compared to baseline and to the waitlist control group. We also expect the intervention to have a positive effect on both work-related and non-work performance. Namely, we expect participants to report higher job performance and organizational citizenship behavior at work and increased family role performance in the non-work domain during and after the intervention compared to baseline and to the waitlist control group. Additionally, we will explore, whether variables such as proactive personality, focus on opportunities, selection, optimization, and compensation strategies, need strengths, home and job demands, job crafting and off-job time activities have a role in participants’ engagement in different off-job crafting behaviors and its effects to their well-being and performance in different life domains.

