**Fig. 1 Fig1:**
[figure not shown]
Off-job crafting intervention design

The study will be carried out in Finland from October 2019 to May 2020. All participants who have given informed consent to participate in the study will first fill out an online baseline questionnaire, concerning demographics (e.g., age, gender, education), basic job information (e.g., work hours), off-job and job crafting, psychological needs, well-being (e.g., mental fatigue, work engagement) and performance (e.g., family role performance, organizational citizenship behavior) 2 weeks before the intervention period. Additionally, intervention group participants will receive a small task to complete before the first training session. The task consists of composing a list of things that the participant likes and dislikes doing during their off-job time. In addition, they are asked to take two picture that represent: 1) an activity that they loved doing over the past week and 2) an activity that they did not like to do during their off-job time. One week before the first training session, participants will receive a reminder to complete the questionnaire and the homework task. Two weeks after the baseline measurement, intervention group participants will take part in a half-day long training session. Shortly before the training, each intervention group participant receives a personal feedback report containing information about their baseline scores on DRAMMA needs satisfaction and comparison of their scores to reference values derived from other published scientific studies with Finnish and European knowledge workers as the reference group [23–25]. During the four-week intervention period, every Tuesday, intervention group participants will receive an email with a link to a weekly online questionnaire. In case of non-response, reminders will be sent on Wednesdays and Thursdays. The control group will be asked to fill out a second questionnaire immediately after the end of the intervention period of the intervention group. Additionally, participants from both groups will receive the same online questionnaire via email twice during the post-intervention period (two and six weeks after intervention). After the intervention period, the intervention group will participate in a half-day long reflection session.

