After the psychological needs training, participants will be asked to choose one psychological need that they wish to focus on during the four-week intervention period. While they are free to choose whichever of the six needs they want to work with, we recommend aiming to work with the psychological need that they scored the lowest on. This recommendation is made to support more balanced needs satisfaction across different needs, which has been found to be associated with higher reported well-being [32]. Participants will work in small groups and will be assisted by trainers to come up with their individual SMART off-job crafting goals. In the end, they will write their goals down in their personal booklets. As forming implementation intentions has been shown to improve goal achievement [33], participants will write a postcard for themselves where they outline how implementing their chosen DRAMMA goal will benefit them, what might potentially interfere with achieving the goal and how to overcome these barriers. The postcards will be sent to the participants during the second week of the four-week intervention as a positive reminder to continue working on their goals.

Next, participants will follow an app tutorial outlining the main functions of the smartphone app Everydaily and create their personal off-job crafting projects in the app. At the end of the first training session, trainers will summarize the main points of the training and the next steps, and participants will have a chance to ask questions about both this training session and the intervention in general.

After the four-week intervention period, participants will attend a second half-day training session. During this session, they first fill out the last weekly questionnaire and will receive new individual needs satisfaction scores, which they can compare to their baseline scores. Next, they have a chance to reflect on their experiences by identifying enablers and barriers that affected their off-job crafting during the intervention period. They will then review their previous goals, set future goals, and have the chance to ask questions. Additionally, we will ask participants to fill out a process evaluation questionnaire at the end of the training session to gather information about intervention reach, dose received and participants’ attitudes toward the intervention [34].

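### Controls answer four questionnaires and the intervention arm seven, so the hypotheses of a difference from control during the intervention can be tested only at its end, and the seven-point change is uncontrolled

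*Protocol article*

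**What the plan says.** All statements are in the protocol article.

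- **Schedule (Study design).** Baseline is common to both arms: "All participants who have given informed consent to participate in the study will first fill out an online baseline questionnaire". The weekly waves are not: "During the four-week intervention period, every Tuesday, intervention group participants will receive an email with a link to a weekly online questionnaire". For controls, "The control group will be asked to fill out a second questionnaire immediately after the end of the intervention period of the intervention group". Both arms then answer two and six weeks after the intervention.
- **Timing of the fourth weekly wave (Training sessions).** The second session follows the four-week period, and of the intervention participants it says "During this session, they first fill out the last weekly questionnaire and will receive new individual needs satisfaction scores".
- **Hypotheses (Background, aim paragraph).** An example is "participants will report higher work engagement and job satisfaction during and after the intervention compared to baseline and to the waitlist control group". Need satisfaction, the non-work well-being outcomes and performance are worded in the same way.
- **Analysis (Effect evaluation).** The first analysis is to "test the change in outcome variables within subjects across seven measurement points before, during and after the intervention", glossed as the "within subject effect of participating in off-job crafting intervention". A second sentence adds a comparison of change over time between the arms. It names neither the occasions nor the coding of time.

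The Measures section speaks of seven questionnaires without separating the arms. Neither Effect evaluation nor Strengths and limitations mentions the unequal schedule.

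**The concern.** Two parts of the protocol do not fit each other. The hypotheses promise a comparison with control during the intervention, and the schedule collects nothing from controls at the first three weekly waves. No later analysis plan can repair this, because the data will not exist.

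The first-listed analysis is a before-after change in one arm. It contains whatever the programme does, but also calendar time (the study runs from October to May) and the effect of answering repeatedly. Calling it an effect of participation invites readers to treat it as evidence of effectiveness, when the randomised comparison is the second, additional analysis.

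The unequal schedule also leaves a trap for the between-arm model. If every wave is used and time enters as a straight line, the two slopes are fitted on different sets of occasions. A curved trend that both arms share then gives different fitted slopes, even with no treatment effect.

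**Working it through.** **1. Occasions per arm.** Weeks are counted from the start of the intervention. Baseline is two weeks before it (Study design). Placing the weekly waves at weeks 1 to 4 is an assumption.

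| Occasion | Week | Intervention | Control |
|---|---|---|---|
| Baseline | -2 | yes | yes |
| Weekly 1 | 1 | yes | no |
| Weekly 2 | 2 | yes | no |
| Weekly 3 | 3 | yes | no |
| Weekly 4 / control's second | 4 | yes | yes |
| Two-week follow-up | 6 | yes | yes |
| Six-week follow-up | 10 | yes | yes |

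Intervention: 1 + 4 + 2 = 7, which reproduces the plan's seven. Control: 1 + 1 + 2 = 4.

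**2. What can be estimated.** A full group-by-occasion model has 2 × 7 = 14 means. Observed cells are 7 + 4 = 11, and the design matrix has rank 11. The missing three are the control means at weekly waves 1 to 3. Of six post-baseline contrasts with control, three can be estimated (end of intervention, two weeks, six weeks) and three cannot, whatever the coding of time.

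The end-of-intervention contrast is approximate but usable. Both arms answer just after the four weeks, and most items ask about the past week, so both describe roughly the last intervention week.

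**3. Sample size used below.** The plan's effect size of 0.25, read as Cohen's f for two groups, is d = 2 × 0.25 = 0.5. The normal approximation gives 63 per arm. The exact t calculation gives 64, with power 0.801. The plan's 64 is reproduced and used here.

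**4. Illustration of the conditional bias.** Assumptions, none of them from the protocol: no treatment effect; both arms shift by the same amount δ from baseline to every later wave; total SD 1; within-person correlation 0.5; linear time with a random intercept.

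For such a step, the fitted slope in an arm is (mean time − baseline time) × δ / S, where S is the sum of squared deviations of that arm's times.

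- *Time in weeks.* Intervention: mean 24/7 = 3.429, S = 87.71, slope 5.429/87.71 = 0.0619δ. Control: mean 4.5, S = 75, slope 6.5/75 = 0.0867δ. Difference −0.0248δ per week; × 12 weeks = −0.297δ.
- *Wave number, common numbering (0 to 6 against 0, 4, 5, 6).* Intervention: 3/28 = 0.1071δ. Control: 3.75/20.75 = 0.1807δ. Difference −0.0736δ per wave; × 6 = −0.441δ.

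The standard error of the slope difference is √[(1 − 0.5)/64 × (1/S₁ + 1/S₂)].

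- *Weeks:* √[0.0078125 × (1/87.71 + 1/75)] = 0.0139. With δ = 0.5 the spurious difference is −0.0124, so z = −0.89 and rejection is about 14.5%. Simulation with 2,000 replicates gave 13.8%.
- *Wave number:* √[0.0078125 × (1/28 + 1/20.75)] = 0.0256. The spurious difference is −0.0368, so z = −1.44 and rejection is about 30%. Simulation gave 31.9%.
- *Four shared occasions:* the slopes are equal and the bias is 0. Simulation gave 4.9%.

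**5. Sensitivity to the assumed shape** (time in weeks, correlation 0.3 to 0.7, shared change of 0.5 SD).

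| Shared trend | Spurious effect over 12 weeks | Type I error |
|---|---|---|
| Flat or linear | 0 | 5% |
| Early plateau (same as the step at these times) | −0.15 SD | 12–21% |
| Dip in weekly waves 1–3 only | +0.29 SD | 32–62% |
| Quadratic peak | −0.11 SD | 9–14% |

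If waves were numbered separately within each arm (0 to 6 against 0 to 3), even a linear shared trend of 0.5 SD would give −0.087 SD per wave and a type I error of 40–74%. With categorical time and group terms only at the three shared post-baseline occasions, the bias is 0 for every shape tried.

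**The case against.** Three stronger readings are tempting, and the protocol does not support them.

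*That there is no control comparison for the intervention period at all.* The control arm's second questionnaire lines up approximately with the fourth weekly one, so one contrast exists. Only weekly waves 1 to 3 are lost.

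*That the planned group-by-time test is biased.* The seven points belong to the sentence on within-subject change. The between-arm test is a separate sentence that commits to no set of waves and no straight line. Unequal occasions do not in themselves bias a multilevel model: with time in weeks and a flat or linear shared trend, the bias is zero. An article may also leave the coding of time to a fuller plan, so its absence is not itself a fault.

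*That every outcome, or half of the hypotheses, is affected.* For off-job crafting itself, the Background ties the comparison with control to a between-person difference and the intervention period to a change from before. The mismatch concerns need satisfaction, well-being and performance, and no count supports a half.

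Nor is regression to the mean a strong argument here. No selection on low scores is stated, and the advice to work on the lowest-scoring need comes after baseline and does not shift arm means on the other outcomes.

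What stands against these defences is the conflict between hypotheses and schedule, which no choice of model removes, and the label on an uncontrolled change. The article does separate the within-subject from the between-subject effect, but it still attributes the former to participation.

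**Conclusion.** The point holds in two parts that need no assumption. First, the hypotheses of a difference from the waitlist group during the intervention can be tested only at its end; three of the six post-baseline contrasts have no control data. Second, the seven-point within-subject change is available in the intervention arm alone and cannot be read as an effect of the programme.

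The third part is a warning and not a demonstrated error. Depending on how time is coded, a shared non-linear trend could enter the group-by-time estimate. The 14% and 32% rest on an assumed shared step of 0.5 SD, a correlation of 0.5 and 64 per arm. A step that large equals the effect the trial is powered for. The direction also depends on shape: a shared early rise makes the intervention look worse on an outcome where higher is better, and a temporary dip makes it look better. One outcome has a visible possible source of a step, because off-job crafting is measured with 18 items at baseline and 6 afterwards; the protocol gives no size for it.

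**What to change.** 1. In Effect evaluation, define the randomised analysis as group by categorical time on the four questionnaires that both arms complete, with contrasts against baseline at end of intervention, two weeks and six weeks.
2. In the Background, limit the comparison with the waitlist group during the intervention to the end-of-intervention contrast. Alternatively, send controls the same weekly e-mailed questionnaire.
3. Report the seven-wave trajectory of the intervention arm as descriptive, and drop the wording that makes it an effect of participating.
4. State in Measures which questionnaires each arm receives.

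The cost is a change of wording and a simpler model. The price is that no randomised claim can be made about weeks 1 to 3. The alternative in item 2 costs three more questionnaires for each control participant. It would also equalise the amount of questioning, which otherwise differs by three questionnaires and cannot be separated from treatment even on the shared occasions.
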